Positive Parenting	Parenting Self-Efficacy, 4-items from PSI-SF		X	X	X	X
Social Support	Social Support Effectiveness Questionnaire		X	X	X	X

**Fig. 2 Fig2:**
[figure not shown]
Participant Timeline

This trial protocol reporting adheres to the Standard Protocol Items: Recommendations for Intervention Trials (SPIRIT) guidelines [38] and was registered with ClinicalTrials.gov. All procedures will be performed in accordance with the Research Ethics Board at the University of Manitoba, Fort Garry campus and the 1964 Helsinki Declaration and its later amendments. All participants will provide informed consent prior to enrolment in the study.

## Methods: participants, interventions and outcomes

### Study setting {9}

The intervention will be delivered through an app-based psychoeducation platform, hosted in Canada on secure Google Cloud Services in the Montréal Google Cloud Platform Region. Assessments (T0-T4) will be conducted online via the Research Electronic Data Capture (REDCap) tools for Personal Health Information Act (PHIA) compliance and data security [39–41].

### Eligibility criteria {10}

#### Inclusion and exclusion criteria

Eligibility includes: identifying as a parent with a child aged 24–71 months, English speaking, at least the age of 18 years, and residing in Manitoba, Canada. Parents must also self-report: moderate-to-severe symptoms of depression (≥ 10) on the Patient Health Questionnaire (PHQ-9) [42], and/or anxiety (≥ 10) on the General Anxiety Disorder (GAD-7) scale [43], and/or clinical levels of parenting stress (total score ≥ 110, parental distress subscale ≥ 38, parent–child dysfunctional interactions subscale ≥ 31, difficult child subscale ≥ 38) on the Parenting Stress Index – 4 th Edition – Short Form (PSI-4-SF)) [44], and/or clinical levels of anger (≥ 16) using the Patient-Reported Outcomes Measurement Information System (PROMIS-Anger) [45] at time of enrolment (T0). Parents with no self-reported symptom scale elevations but who are otherwise eligible will meet with a member of the BEAM team to determine eligibility. This eligibility decision will be based on clinical judgement, ensuring that those with need can participate. Eligible parents will be asked if they are available and willing to join the 12-week program and whether they can participate in regular individual check ins (15 to 60 min) via videoconference, phone, or direct messaging with a peer coach.

In terms of exclusion criteria, given that the BEAM program is not designed to support the needs of individuals at high risk for suicide and/or self-harm, parents who report self-harm that required medical attention within the past six months, a suicide attempt within the past year, or active thoughts of suicide with a plan will be ineligible without additional supports in place. These parents must be engaged in or on a waitlist for individual therapy with a psychiatrist, psychologist, social worker, or regulated mental health professional for the duration of their BEAM involvement. Parents at risk for suicide or self-harm who are not actively engaged in individual therapy will meet with a member of the BEAM team to be connected with or placed on a waitlist for these services before engaging in the BEAM program. Individuals who have participated in prior versions of the BEAM program will be excluded.

#### Screening and enrolment

After informed consent for the screener is obtained, prospective participants will be asked to complete an online eligibility screener to confirm that they are 18 years or older, speak English, have at least one child between 24 and 71 months, meet the threshold for depression, anxiety, parenting stress, and/or anger, respectively, and are willing to complete check ins with a peer coach (T0). Participants will be considered enrolled after they consent to participate in the study, complete the pre-test assessment, and participate in an orientation meeting with their peer coach and/or a member of the research team (T1). Individuals who do not meet the eligibility criteria will be excluded.

### Who will take informed consent? {26a}

Prospective participants who agree to be involved in the study will read an online informed consent form explaining the study procedures in full detail and will provide electronic written consent. Prospective participants will have the option to contact the research coordinators through the BEAM program email address should any questions regarding the informed consent form arise.

## Interventions

### Intervention description {11a}

The BEAM Program is built upon mHealth best practices and evidence-based program design principles, with the core objectives of improving parental mental health and fostering supportive parenting. The program's delivery will be facilitated through a mobile application, developed and overseen by MindSea. The BEAM program is a 12-week app-based mental health and parenting intervention, appropriate for the treatment of transdiagnostic emotion-based mental health symptoms (e.g., mood, anxiety, anger). In the 12-week self-guided BEAM program, participants will complete modules with a cohort of 40 to 80 parents. Each week includes: (a) 15–20 min of therapeutic video content, (b) exercises to practice key skills, (c) access to the online forum to cultivate social support through interaction with other parents and peer coaches, (d) individual check ins with peer coaches (i.e., trained and supervised staff with lived experience, employed by the University of Manitoba) via videoconference, phone, or direct messaging, lasting between 15 to 60 min depending on needs and preferences of participants, (e) a brief in-app survey for symptom monitoring to track progress across well-being and parenting metrics. Over the course of the program, participants will be invited to optional group drop-in sessions (e.g., tea and chat) facilitated by peer coaches on Zoom for Healthcare to connect and discuss program content and/or invite experts to discuss and answer questions for topics of interest identified by participants. Participants will also be connected with a Systems Navigator who can support them in accessing other resources (e.g., childcare programs, legal aid, housing) within their community. Peer coaches will be supervised at arm’s length by our clinical research team and will monitor the forums (i.e., encourage discussion, provide support) and lead all check ins with participants. The clinical research team will train peer coaches to flag signs of acute mental health risks, such as suicidal ideation, in which case the clinical team will assess the next steps for supporting the parent (e.g., crisis support resources). Additionally, peer coaches will be trained to deliver the BEAM program with fidelity by the research team (including recruitment, enrolment, participant tracking, coaching, and all aspects of delivery) using materials we have developed. The BEAM program aims to address the pressing need for accessible and effective mental health interventions by adopting a stepped care model. Stepped care is a comprehensive framework that offers a structured approach to providing mental health services in a tiered manner, ensuring that participants receive appropriate levels of support based on the severity of their needs. Within BEAM, at the heart of this model are peer coaches, who will have the most direct contact with participants. Peer coaches will monitor the online forum, facilitate individual check ins, and facilitate group drop ins. Peer coaches are supervised directly by a registered clinical psychologist, and will be trained to escalate concerns to our clinical team (i.e., clinical psychologists, senior students in clinical psychology) as needed.

Core components of the BEAM program are more thoroughly described below:

Each week, 15 to 20 min of therapeutic video content will be released on the BEAM mobile application. Videos will consist of psychoeducational parenting and mental health content. Parenting content was developed by [name] using emotion-focused parenting, parent management training, and attachment parenting theoretical orientations. Mental health content was developed by [name] and [name] drawing from transdiagnostic emotion-focused mental health and third wave Cognitive Behavioural Therapy principles such as Dialectical Behavioural Therapy, Acceptance and Commitment Therapy, and the Unified Protocol. Short weekly exercises will be released within the app alongside the therapeutic video content. Participants will be able to open the exercises and complete it using their device. The purpose of these exercises is to allow for the opportunity to practice key skills and consolidate program content.

Participants will complete a brief survey every week (i.e., modified symptom rating sliding scale, see Appendix 1; Appendix 2) within the BEAM app for symptom monitoring and feedback informed treatment. Each completed weekly survey will populate a graph in the app, displaying the trends of the participants’ symptom scores over time. This graph is visible to researchers, participants and their peer coach and can be discussed during check ins.

Each participant will have individual 15 to 60-min check-ins with a peer coach. These check-ins will occur at a frequency defined by the participant in consultation with the peer coach, and may occur anywhere from weekly to monthly. The first check-in of the program will be an orientation, where program goals are reviewed and participants can have their questions answered. Subsequent check ins will have coaches asking participants how they are feeling as they progress through the program materials and content. These check-ins are intended to support program progression and to answer any program-related questions. Participant attendance at these check ins will be tracked. Check-ins will take place through Zoom for Healthcare, phone, or direct messaging based on participant preference, needs, and availability. Participants will schedule their check-in using the scheduling software Calendly. Participants will be sent a link with the peer coach’s monthly availability and will be asked to input their first name and personal email to schedule an appointment. Calendly invitee data (i.e., first name and email) is hosted by Google and Amazon Web Services in the United States. Calendly data will not be linked to the BEAM app or BEAM data in any manner.

Participants will also have access to the app-based online forum to cultivate social support through interaction with other parents and peer coaches. The forum will be monitored by peer coaches who will also be active in the forum providing support and prompting discussion. Peer coaches will also facilitate optional drop-in groups via Zoom for Healthcare to provide an additional opportunity for participants to connect with peers and discuss program content.

All participants will be connected to a Systems Navigator who can support participants in accessing a wide variety of services. The Systems Navigator can connect participants to community resources such as housing supports, couples counselling, fun kids summer activities, culturally aligned resources and programming, and meet ups at community centres for to support ongoing relationship building. To ensure that the implementation of this Systems Navigator service aligns with the needs of our community partners, we hosted a Knowledge Exchange event with front-line service providers and community workers. At this event, we discussed the acceptability and feasibility of connecting their organizations and/or resource centres with a Systems Navigator. We will work to implement their feedback to ensure the Systems Navigator role appropriately supports parents and families. Additionally, we are building reciprocal relationships with community organizations where they will recommend parents to the BEAM program and our System Navigator will recommend parents back to their organizations for community services.

### Criteria for discontinuing or modifying allocated interventions {11b}

Should participants disclose suicidal behaviour, peer coaches will notify the clinical team. The clinical team will meet independent of the peer coaches to advise on whether or not continued participation in the BEAM program is in the best interest of the participant. In accordance with Best Practice Guidelines for Telepsychology Services, clinical research staff may also decide to terminate a participant’s involvement in the mHealth program if they deem it inappropriate for the participant to continue (e.g., if the participant cannot ensure confidentiality is maintained through access to a secure space and stable internet connection) [46]. Furthermore, participants may have discontinued access to the forum and may be denied access to the drop-in sessions if they engage in repeated violations of the terms of use. In these cases, participants would still have access to psychoeducation materials and would still be invited to do the assessments. The peer coaches may also provide a referral to another provider or clinic if deemed appropriate.

### Strategies to improve adherence to interventions {11c}

The proposed trial incorporates strategies such as reminders via in-app messaging, email, and telephone (SMS), which have also been shown to increase engagement [47]. Participants will be contacted through email by their peer coach if they have not attended check ins or engaged with the program material. Peer coaches will also be assigned to facilitate and promote participant engagement on the forum.

### Relevant concomitant care permitted or prohibited during the trial {11 d}

Participants will be permitted to receive concomitant care for mental health problems, such as psychotherapy, medication, and/or support groups. No concomitant care and interventions are prohibited. Concomitant care and interventions will be measured so they can be controlled for in analyses.

### Provisions for post-trial care {30}

If further treatment is deemed necessary, a referral to another provider or clinic will be made, and a list of community services will be provided.

### Outcomes {12}

#### Primary outcomes

This trial has co-primary aims evaluating: (1) BEAM’s effectiveness in improving parent mental health outcomes, and (2) the implementation of BEAM in the community through metrics of feasibility, acceptability, and uptake.

The co-primary effectiveness outcome is mean change in a composite score of parent mental health symptoms across all four timepoints: pre-intervention (T1), post-intervention (T2), 6-month follow-up (T3), and 12-month follow-up (T4). This composite score will be defined uniquely for each participant using a weighted average of their pre-intervention (T1) mental health profile (i.e., self-report symptoms of depression, anxiety, anger, and sleep problems). Pre-intervention symptoms above established clinical cut-offs will be mean-centred, standardized, and included in the participant’s composite mental health symptom score weighted by the symptom’s pre-intervention severity. In this way, the primary outcome will track mean change in each participant’s most clinically elevated pre-intervention symptoms. Depressive symptoms will be assessed using the PHQ-9 [42], a 9-item self-report measure of depression severity. Each item taps the frequency of depressive symptoms over the past week on a 4-point Likert scale (0 = *not at all* to 3 = *nearly every day*). Total scores range from 0 to 27, with higher scores indicating greater depressive symptom severity. A PHQ-9 cut-off score of ≥ 10 will identify participants with clinically elevated symptoms of depression. Anxiety symptoms will be assessed using the GAD-7 [43], a 7-item self-report measure of anxiety severity. Each item taps the frequency of anxiety symptoms over the past week on a 4-point Likert scale (0 = *not at all* to 3 = *nearly every day*). Total scores range from 0 to 21, with higher scores indicating greater anxiety symptom severity. A GAD-7 cut-off of ≥ 10 will identify participants with clinically elevated symptoms of anxiety. Anger will be assessed using the PROMIS Short Form, a 5-item self-report measure of anger frequency and severity [45]. Total scores range from 5 to 25, with higher scores indicating more anger. A PROMIS cut-off ≥ 16 will identify participants with clinically elevated anger symptoms. Sleep problems will be measured using the PROMIS Sleep Disturbance Scale, an 8-item self-report measure of sleep disturbances [48]. Total scores range from 8 to 40, with higher scores indicating greater severity of sleep disturbance. A PROMIS Sleep Disturbance Scale cut-off ≥ 30 will identify participants with clinically elevated sleep disturbances. All outcome measures are outlined in Table 1. We have obtained the necessary licenses to use all instruments mentioned in the protocol, ensuring compliance with their respective copyright and usage requirements.

The co-primary implementation metrics of feasibility, acceptability, and uptake when BEAM is implemented in the community will be assessed relative to previous trial benchmarks. Feasibility of the BEAM program will be assessed at post-intervention using the mHealth App Usability Questionnaire (MAUQ) [49] and other questionnaires developed for the BEAM program. Acceptability and uptake of the BEAM program will be assessed in three ways: (1) rates of recruitment, retention, (2) qualitative analysis of responses to post-intervention focus group questions that probe barriers and facilitators to program engagement, and (3) general program engagement measures from back-end app data. A list of implementation outcomes are outlined in Table 2.

**Table 2 Tab2:** BEAM Implementation and Engagement Measures

Construct	Metric

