### Assignment of interventions: allocation

Not applicable, there will be no assignment to different interventions.

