## Statistical methods

### Statistical methods for primary and secondary outcomes {20a}

Analysis of the primary outcome (parent mental health symptom composite) will examine change across all four timepoints: pre-intervention (T1), post-intervention (T2), 6-month follow-up (T3), and 12-month follow-up (T4). A two-level linear mixed effects model with random slopes will evaluate the hypothesis that parent mental health symptoms will evidence significant reductions from T1 to T2, T1 to T3, and T1 to T4. This model will account for sociodemographic and socioeconomic factors as well as other theoretically- and empirically-motivated covariates [69]. Baseline mental health symptom severity (T0) will be examined as a baseline moderator. Other theoretically- and empirically motivated exploratory baseline moderators of change may also be examined. The same two-level linear mixed effects modelling approach will evaluate change in secondary outcomes (i.e., individual parent mental health symptoms, parenting behaviours, child mental health and development). All data will be included following an intention-to-treat approach, where missing data will be handled using full information maximum likelihood estimation. Sensitivity analyses will be used to examine complete-case methods should the assumption of missing at random be met. Analyses will be led by the research team, in consultation with the Centre for Healthcare Innovation, using MPlus v8.0. The research team will also investigate if there is baseline (T0) moderation by symptom severity to examine whether the BEAM intervention is more effective for participants who have higher symptom levels before receiving the intervention (e.g., depression, anxiety, anger, sleep disturbances).

To measure the impact of BEAM via implementation metrics and cost-effectiveness we will use benchmark uptake and attrition markers, to determine the extent to which the BEAM program succeeds on key implementation metrics including acceptability, feasibility, fidelity, cost, and sustainability [70]. Mixed-methods data from agency perspective, app usage, and user experience will inform continuous improvements using implementation metrics we have used in the past including app, group and coach engagement as well as user satisfaction. Quantitative data related to app usage and UX data will be linked to outcome variables to elucidate what components of program engagement are associated with symptom remission.

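### The primary composite selects and weights symptoms on the same T1 scores from which change is measured, so a fall from T1 is expected even if BEAM has no effect

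*Protocol article*

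**What the plan says.** Under Primary outcomes, the composite is personal to each parent: "This composite score will be defined uniquely for each participant using a weighted average of their pre-intervention (T1) mental health profile". The four candidate symptoms are depression (PHQ-9, cut-off 10), anxiety (GAD-7, cut-off 10), anger (PROMIS, cut-off 16) and sleep (PROMIS, cut-off 30). The rule is that "Pre-intervention symptoms above established clinical cut-offs will be mean-centred, standardized, and included in the" parent's composite, each "weighted by the symptom’s pre-intervention severity". The stated purpose is that "the primary outcome will track mean change in each participant’s most clinically elevated pre-intervention symptoms".

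Under Statistical methods {20a}, the hypothesis is that "parent mental health symptoms will evidence significant reductions from T1 to T2, T1 to T3, and T1 to T4", tested in a two-level mixed model with random slopes. T0 severity appears there only as a moderator.

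The trial is single-arm. On allocation the article says: "Not applicable, there will be no assignment to different interventions". The two matched cohorts are for administrative-linked outcomes and do not provide the self-report scales. Table 1 shows PHQ-9, GAD-7 and PROMIS Anger collected at T0 (screening) and again at T1. Sleep starts at T1.

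**The concern.** T1 does three jobs: it decides which symptoms enter, it sets their weights, and it is the reference for change. A scale that is high at T1 partly by chance is kept and up-weighted; one that is low partly by chance is dropped. At the next measurement the chance part is redrawn, so the retained scales fall on average without any treatment effect. No comparator cancels this.

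The design had a natural protection. Eligibility is applied at T0 and change is measured from a second measurement at T1, so much of the regression caused by screening is spent before the baseline. Selecting again on T1 gives that protection up.

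At stake is the co-primary effectiveness test, whose result is meant to inform readiness for nationwide scaling.

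**Working it through.** **The plan's own figure.** N = 400 (alpha 0.05, power 0.80, 30% attrition) cannot be reproduced, because Sample Size gives no numeric effect, SD or correlation. For orientation, treat the test as a simple paired change, two-sided. Completers: 400 × 0.70 = 280. Detectable standardized change: d_z = (1.960 + 0.842)/√280 = 0.167 (0.140 with all 400).

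**Inputs from the protocol.** The four cut-offs and score ranges, selection and weighting on T1, eligibility applied at T0, and 280 completers. For sleep I used the 8-to-40 range in Primary outcomes (Table 1 labels the form 4a).

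**Assumptions, not in the protocol.**
- Retest correlation r = 0.6 to 0.9, equal between all occasions.
- Cross-symptom correlation 0.5 or 0.7.
- Applicant mean/SD before screening: PHQ-9 10/5.5, GAD-7 9.5/5, Anger 13.5/4.2, Sleep 25/6.5 (near the cut-offs), or all means 1 SD higher.
- Weight: the T1 score's position within the scale range. The protocol does not define the weight; a steeper one would enlarge the fall.
- No treatment effect and no time trend.

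**Method.** Simulate 400,000 applicants at T0, T1 and T2, screen on the three symptom scales at T0, build the composite from T1 as written, and take the T2 minus T1 change in T1 SD units. Chance of a significant fall = Φ(|d_z|·√n − 1.96), where n = 280 × the share of parents with a composite.

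**Results under no effect** (mean change in T1 SD; |d_z|; chance of a significant fall):

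| Cross-corr., means | r = 0.6 | r = 0.7 | r = 0.8 | r = 0.9 |
|---|---|---|---|---|
| 0.5, near cut-offs | -0.31; 0.40; >99.9% | -0.23; 0.33; 99.9% | -0.15; 0.26; 98% | -0.08; 0.17; 79% |
| 0.7, near cut-offs | -0.28; 0.34; 99.9% | -0.21; 0.28; 99% | -0.14; 0.22; 92% | -0.07; 0.15; 64% |
| 0.5, 1 SD higher | -0.15; 0.21; 93% | -0.11; 0.18; 84% | -0.07; 0.14; 62% | -0.04; 0.10; 37% |
| 0.7, 1 SD higher | -0.12; 0.16; 74% | -0.09; 0.14; 60% | -0.06; 0.11; 41% | -0.03; 0.07; 21% |

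Two entries worked through:
- Cross-correlation 0.5, near cut-offs, r = 0.8: 88.1% have a composite, so n = 280 × 0.881 = 247. Then 0.255 × √247 = 4.00, and Φ(4.00 − 1.96) = Φ(2.04) = 98%.
- Smallest case (0.7, 1 SD higher, r = 0.9): n = 280 × 0.976 = 273. Then 0.070 × √273 = 1.16, and Φ(1.16 − 1.96) = Φ(-0.80) = 21%.

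**What drives it.** With equal weights on the same T1-selected symptoms, means near the cut-offs and cross-correlation 0.5, the fall is -0.29 to -0.07 instead of -0.31 to -0.08. The T1 cut-off does most of the work and the weights add a little. Standardizing within each timepoint leaves it almost unchanged. It vanishes only at r = 1. With r equal between all occasions, the expected fall to T3 and T4 is the same as to T2; if correlation decays with time, it is larger.

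**Comparators under the same null.** The average of all four scales for every parent changes by about 0.00, with a 2.5% to 2.9% chance of a significant fall. A three-scale composite (PHQ-9, GAD-7, anger) selected and weighted on T0 also changes by about 0.00 (2.5% to 2.7%). The same three scales selected on T1 give -0.07 to -0.29 and 71% to over 99%, so the result does not depend on the sleep scale.

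**Parents without a composite.** With means near the cut-offs, 8% to 20% of simulated parents are below every cut-off at T1, before counting those admitted on parenting stress or clinical judgement. {20a} says that all data will be included under intention-to-treat.

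**The case against.** The size is not known. No retest correlation, mean or SD is in the document, and case-mix matters a great deal: at r = 0.8 and cross-correlation 0.5, moving the means up by 1 SD takes the false-positive chance from 98% to about 62%. This stands, and is why a range is given.

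A reader might infer that a significant result is guaranteed. It is not. Only the direction of the expected change is certain, and only with r below 1 and no opposing worsening.

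A reader might also infer that the artefact is as large as the effect sought. The document cannot support that, because it describes the effect only as moderate and then about 25% smaller. If moderate is taken as 0.5, the target is 0.5 × 0.75 = 0.375, and in change-SD units the artefact reaches that size only at the lowest retest correlation with means near the cut-offs.

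Nor is the hypothesis beyond refutation. PHQ-9, GAD-7, anger and sleep are each planned as secondary outcomes in all participants, without T1 selection. If BEAM did nothing, those scales would stay flat beside a falling composite. That cross-check exposes the discrepancy but does not repair the primary test.

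Finally, an analysis plan not shown here may add detail. The composite, however, is defined in the article itself, so this is a stated rule and not an omission. Covariates, random slopes, T0 moderation and maximum likelihood do not undo selection on the baseline.

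**Conclusion.** The point holds: the primary composite as defined has a built-in expected fall from T1 under no effect. Across the assumptions above, the spurious T1-to-T2 change is about -0.03 to -0.31 T1 SD. The chance of a false significant fall is about 20% to over 99% (about 60% to over 99% with means near the cut-offs), against a nominal 2.5%. These figures also rest on a paired-change approximation to the mixed model. The rule separately leaves some parents without a primary outcome, in conflict with the intention-to-treat statement. Because this is the co-primary effectiveness endpoint, it should be corrected before the primary analysis.

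**What to change.** Before analysis, define the primary composite for every parent as the plain average of PHQ-9, GAD-7, PROMIS Anger and PROMIS Sleep, each standardized at all timepoints by the full-sample T1 mean and SD. Fixing the T1 values matters, because standardizing separately at each timepoint would also remove a real mean change. Keep the T1-selected composite as descriptive only.

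If a personalised composite is wanted as a supporting analysis, select and weight PHQ-9, GAD-7 and anger on T0 scores and measure change from T1. State its limits: sleep has no T0 score; parents admitted on parenting stress or clinical judgement may have no elevated T0 symptom; and a small residual fall remains if correlation decays with time.

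Do not use the T0-to-T1 change as a no-programme benchmark. Eligibility is applied at T0, so that change carries screening regression: about -0.04 to -0.24 SD per scale in the null case with means near the cut-offs, while T1-to-T2 is zero.

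Cost: an amendment and analysis code, with no new measures. Trial Status puts completion of primary measures at January 2027, so there is time. Since steering committee agendas include preliminary outcome reporting, the amendment should be dated and say what had been seen. The price is a smaller effect estimate and a composite no longer focused on each parent's most elevated symptoms, which is a design decision and not only wording. The change removes this artefact; natural recovery and other single-arm confounding remain.
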